### Statistical methods

Patient characteristics will be summarized using means (± standard deviation) or medians (interquartile range) for continuous variables and counts (percentages) for categorical variables.

A non-inferiority analysis will be conducted to evaluate whether standard precautions are non-inferior to contact precautions with respect to the incidence density (per 1,000 patient-days) of hospital-acquired ESBL-E. The non-inferiority margin is set at Δ = 1 additional acquisition per 1,000 patient-days.

The primary analysis will compare ESBL-E acquisition incidence rates between SP and CP periods using a count regression model (Poisson or negative binomial in case of overdispersion), with log(patient-days) included as an offset. Models will include fixed effects for intervention (SP vs CP), calendar period or season, and period order. Additional adjusted analyses will include systemic antibiotic exposure during hospitalization as a covariate to account for antimicrobial pressure as a potential confounding factor. Marginal incidence rate differences (SP − CP, per 1,000 patient-days) and their one-sided 95% confidence intervals will be derived from the fitted models. Non-inferiority will be concluded if the upper bound of the one-sided 95% confidence interval is below the predefined margin.

All analyses will be performed using SAS version 9.3 (SAS Institute, Cary, NC, USA).

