**Methods and analysis:**

We will conduct a prospective, two-site interventional study in two geriatric departments of the Metz–Thionville Regional Hospital Center (Metz, France) using an alternating-period (crossover-like) design at the site level, with random allocation of the starting condition (CP first vs SP first).

Patients will be screened for ESBL-E carriage at admission and at discharge. During CP periods, contact precautions are implemented only for patients with clinically detected ESBL-E infections identified through routine clinical cultures; asymptomatic ESBL-E carriage identified through surveillance screening does not trigger contact precautions. During SP periods, patients are managed using SP alone.

The primary outcome is the incidence density of ESBL-E acquisition per 1,000 patient-days. Secondary objectives include species-specific analyses comparing ESBL-producing Escherichia coli and non-E. coli Enterobacterales. The total inclusion period is four years. Incidence rates will be compared using count regression models adapted to clustered period-based data.

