### Randomization

The order of implementation of the two study periods (CP and SP) is randomly assigned at the site level. Each participating site is allocated to one of two possible sequences (CP followed by SP, or SP followed by CP) using simple randomization with a block size of two, to ensure different initial sequences across sites.

The randomization sequence is generated by the methodologist of the Clinical Research Support Platform at the Metz–Thionville Regional Hospital Center and stored in a secure electronic file. The allocation sequence is communicated to the investigators prior to study initiation.

The organization of the intervention according to study site and randomized period order is illustrated in Figure 3.

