### Sample size

Based on a study conducted in an acute geriatric unit at a Belgian teaching hospital [31], we assumed an incidence density of 1 hospital-acquired ESBL-E acquisition per 1,000 patient-days during CP periods. The non-inferiority margin was set at 1 additional acquisition per 1,000 patient-days, based on a previous prospective non-inferiority study conducted in the intensive care unit of the same hospital institution evaluating discontinuation of contact precautions for MRSA and ESBL-E [29]. This threshold was considered clinically acceptable for the present pragmatic infection prevention study. Using a one-sided alpha of 5% and 80% power, a total of 6,178 patient-days were required.

After accounting for clustering using an intra-cluster correlation coefficient of 0.003 [32] and a design effect of 1.48 [33], the required sample size increased to 9,130 patient-days.

Based on an average length of stay exceeding four days, a total of 954 patients will be included to achieve the required number of patient-days, accounting for an anticipated 15% exclusion rate.

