## Discussion

### Limitations and interpretation

This pragmatic interventional study evaluates infection prevention and control policies under real-world conditions in an understudied acute geriatric setting. Several limitations should be considered when interpreting the findings.

First, the intervention evaluated in this study corresponded to an infection-triggered CP strategy rather than systematic isolation of all ESBL-E carriers. Consequently, the findings should therefore be interpreted within the context of routine clinical practice in acute geriatric care.

Second, allocation occurred at the site level, with only two participating hospital sites serving as clusters and alternating between CP and SP across study periods. This design limits statistical precision, causal inference, and the generalizability of findings to other healthcare settings. To mitigate this constraint, conservative modelling strategies were pre-specified, period and seasonality effects were accounted for, and sensitivity analyses were conducted. Estimates are therefore interpreted with appropriate caution.

Third, in the absence of systematic in-stay screening, the precise timing and potential source of ESBL-E acquisition during hospitalization could only be approximated using admission and discharge screening. Although this approach allows robust estimation of incidence density, it limits more granular analyses of transmission dynamics and short-term exposure effects.

Fourth, antimicrobial exposure and adherence to IPC practices are recognized drivers of ESBL-E acquisition. Routine clinical microbiological results appropriately guided antimicrobial prescribing, while surveillance screening results were concealed from staff in order to limit behavioural modification during the study. Patient-level antibiotic exposure during hospitalization will therefore be incorporated into adjusted analyses to account for antimicrobial pressure as a potential confounding factor. Measures of hand hygiene compliance and alcohol-based hand rub consumption were also incorporated as process indicators to contextualize the findings. However, residual confounding related to variations in antimicrobial use and prescribing practices cannot be completely excluded.

Co-interventions unrelated to ESBL-E prevention were maintained similarly across study periods in order to limit intervention bias.

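### The primary count model includes between-site-period variation only if an overdispersion check fires, so the non-inferiority bound can be too low

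*Protocol article*

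**What the plan says.** - **Allocation.** Randomization: "The order of implementation of the two study periods (CP and SP) is randomly assigned at the site level". The limitations section describes the study as one "with only two participating hospital sites serving as clusters and alternating between CP and SP across study periods".
- **Sample size.** The size is inflated for clustering: "After accounting for clustering using an intra-cluster correlation coefficient of 0.003 [32] and a design effect of 1.48 [33", which takes 6,178 patient-days to 9,130.
- **Abstract.** "Incidence rates will be compared using count regression models adapted to clustered period-based data".
- **Statistical methods, model terms.** The section lists them as follows: "Models will include fixed effects for intervention (SP vs CP), calendar period or season, and period order".
- **Statistical methods, model family.** Policies are compared "using a count regression model (Poisson or negative binomial in case of overdispersion), with log(patient-days) included as an offset". The marginal rate difference and its one-sided 95% bound come from the fitted model, and non-inferiority is declared if the bound lies below the margin of 1 per 1,000 patient-days.
- **Calendar (under Co-interventions).** Four periods are scheduled at each site. Bel Air runs from spring to early autumn and Mercy from October to March.

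Statistical methods does not say whether the rows are patients or site-periods. It names no variance component or robust variance for site-periods and no small-sample reference distribution. The limitations section says that conservative modelling was pre-specified, but does not describe it.

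**The concern.** Policy changes only from one site-period to the next. Anything else that moves the acquisition rate of a whole site-period, such as an outbreak, colonization pressure at admission or staffing, is therefore noise in the policy contrast. The design pays for this noise through the design effect, but the stated analysis counts it only after an overdispersion finding.

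That safeguard is weak under either data layout. On patient rows each patient has 0 or 1 acquisition, and such data cannot show overdispersion caused by a shared site-period effect. On 8 aggregated counts the negative binomial dispersion would be the right kind of term, but there are too few events for a check to find it.

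One upper bound decides the trial. If its standard error is too small, the error that becomes more likely is declaring standard precautions non-inferior when they are not.

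**Working it through.** **Inputs.** Control rate: "we assumed an incidence density of 1 hospital-acquired ESBL-E acquisition per 1,000 patient-days during CP periods". Margin: "The non-inferiority margin is set at Δ = 1 additional acquisition per 1,000 patient-days". One-sided alpha 5%, 6,178 and 9,130 patient-days, ICC 0.003, design effect (DE) 1.48 and 954 patients with 15% exclusions are all from Sample size. Two sites with four scheduled periods each give 8 site-periods.

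**1. The plan's own inflation.** 6,178 × 1.48 = 9,143, against 9,130 stated (9,130 / 6,178 = 1.478). The step reproduces. Whether 6,178 is itself right is a separate question and is not used here.

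**2. What the listed terms cover.** In the 8-cell layout, a model with intercept, policy and two-level season has rank 3. Adding site leaves the rank at 3, so season is site.
- With a dummy for each of the 8 calendar periods the rank is 8, and it stays 8 when policy is added. Policy is then not estimable.
- With period order as four categories, 6 parameters are fitted to 8 cells, leaving 2 residual df.
- With linear order 4 df remain, and with season alone 5.

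**3. Effect on the bound, by formula.** The standard error is too small by a factor √DE, so the actual one-sided error is 1 − Φ(1.645/√DE).

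| DE | Basis | Actual error |
|---|---|---|
| 1.0 | no site-period variation | 5.0% |
| 1.2 | illustrative | 6.7% |
| 1.35 | 954/8 = 119 per site-period: 1 + 118 × 0.003 | 7.8% |
| 1.48 | plan's figure, √1.48 = 1.217 | 8.8% |
| 2.0 | illustrative | 12.2% |

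At equal rates of 1 per 1,000 and 9,130 patient-days in total (4,565 per policy), the expected bound is 1.645 × √(2 × 0.001/4,565) = 1.09 per 1,000. With DE 1.48 it is 1.09 × 1.217 = 1.32.

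**4. Simulation.** The layout is 8 equal site-periods and 9,130 patient-days, with gamma site-period effects and truth at the margin (CP 1, SP 2 per 1,000). The bound for the marginal rate difference is by the delta method. The squared coefficient of variation (CV²) between site-periods is 0.27 or 0.42:
- 0.27 comes from the ICC. Mean stay is 9,130/(954 × 0.85) = 11.3 days, so patient risk is about 0.011, and 0.003 × 0.989/0.011 = 0.27.
- 0.42 gives DE 1.48 at 1.14 events per site-period (9.13/8).

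With SP at 2 per 1,000 the expected counts are 1.14 (CP) and 2.28 (SP). Weighted by variance, CV² 0.27 then corresponds to a DE of about 1.5 and CV² 0.42 to about 1.8.

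| Analysis | Error, no clustering | Error, CV² 0.27-0.42 |
|---|---|---|
| Poisson, season alone or with linear order | about 5-6% | about 9-14% |
| Poisson, categorical order | about 5% | about 5-7% |
| Cell-rate model, policy + site, t on 5 df | 2-3% | 4-6% |

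A run scaled to DE 1.48 gave 10.3-10.7% for Poisson with linear order. With a dispersion-scaled variance and t on 4 df it gave 2.8-3.0%.

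**5. Would the overdispersion check fire?** Expected events are 9.13 at equal rates and 4.565 × 1 + 4.565 × 2 = 13.7 at the margin. A 5% Pearson test on the 8 counts fired in about one run in ten at equal rates, and in at most about one in five at the margin.

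**The case against.** Four points on the other side have weight.

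**Site is not missing.** A reader might infer from the term list that site is ignored. The calendar does not support that: a two-level season term is the site term. This stands, and it limits the point to variation between periods within a site.

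**The negative binomial option can be a site-period variance.** On aggregated counts it is one, and the abstract's mention of period-based data suggests aggregation. This stands too, so it would be wrong to say that the option can never do the job. What remains is that the layout is not stated and that the term depends on a check that rarely fires with 9-14 events.

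**Variance details belong in an analysis plan.** An article may leave out the estimator and the degrees of freedom, and this one nowhere says that the bound uses Poisson errors with a normal quantile. But Statistical methods does fix the family, offset, fixed effects, interval and decision rule, and it makes extra variance conditional. Someone following that text with no overdispersion finding would use plain Poisson errors.

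**The 8.8% is conditional.** It needs the whole design effect to act between site-periods. ICC 0.003 with DE 1.48 implies 0.48/0.003 + 1 = 161 patients per cluster. That is close to 954/6 = 159 for the six units, and not to 119 per site-period. Stable site or unit differences partly cancel because every site alternates. So 8.8% cannot be stated as the trial's true error, and the possible range starts at 5%.

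**Conclusion.** The point holds in a limited form. The stated primary analysis does not carry through the abstract's promise or the clustering that the sample size assumes, because site-period variation is counted only conditionally and without a small-sample reference.

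If plain Poisson errors are used and site-period variance is not zero, the one-sided error rises from 5% to between 6.7% and 8.8% by formula for design effects of 1.2 to 1.48. In simulation it is about 9-14% with season alone or linear order. Categorical period order nearly removes the excess (about 5-7%), but it leaves 2 residual df and cuts power at equal rates to about 21-25%. The plan's wording on period order allows either coding.

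The result rests on three assumptions: the design effect acts at site-period level, all 8 scheduled site-periods are run, and 9,130 is the total for both policies. Trial status dates the first inclusion to March 2024, after the first scheduled Bel Air period in 2023, so the number of site-periods needs confirming. The documents do not support the stronger conclusions that clustering was never intended or that the bound is too narrow whatever the data show.

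**What to change.** Change Statistical methods to state the following:

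1. **Unit.** The primary analysis uses the 8 site-period counts or rates, with policy, site (which is season) and at most a linear period-order term. It uses no dummy for each calendar period, since policy could not then be estimated.
2. **Variance.** Between-site-period variation is always included and not only after an overdispersion test. Two workable choices are a dispersion-scaled Poisson variance with the scale not below 1, or a linear model for the cell rates with a standard error not below the Poisson one. The second is on the scale of the margin.
3. **Reference.** The bound uses a t quantile on the residual df: 2.015 on 5 df, or 2.132 on 4 df with linear order. If fewer site-periods are run, the df fall accordingly.
4. **Sensitivity.** The plain Poisson or negative binomial model is kept as a sensitivity analysis.

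The abstract, Statistical methods and the limitations section should then describe the same analysis. The change should be made before any data are compared by policy.

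The cost is wording only, plus a wider interval and a lower stated precision. At 9,130 patient-days and equal rates, simulated power of the cell-rate analysis is about 29-31%, against about 45% from the plain Poisson formula without clustering. That both are low is a sample-size matter, separate from this point.

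### About nine expected acquisitions are too few for the large-sample bound from the planned count model: depending on how period order is coded, the bound is often undefined and loses power, or exceeds the stated 5% error

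*Protocol article*

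**What the plan says.** The Statistical methods section compares acquisition rates with a Poisson model, or a negative binomial model if there is overdispersion, with log patient-days as offset. On the terms it says: "Models will include fixed effects for intervention (SP vs CP), calendar period or season, and period order". The marginal SP minus CP rate differences and "their one-sided 95% confidence intervals will be derived from the fitted models", and non-inferiority is concluded if the upper bound lies below 1 per 1,000 patient-days.

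The Sample size section gives the planning values: "we assumed an incidence density of 1 hospital-acquired ESBL-E acquisition per 1,000 patient-days during CP periods", and after the design effect "the required sample size increased to 9,130 patient-days". The schedule under Co-interventions lists four periods at each of two sites, with opposite starting policies. Bel Air runs from spring to autumn and Mercy from autumn to spring.

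The article does not give the expected number of acquisitions, the coding of period order, or what happens when a cell has no acquisitions.

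**The concern.** A regression bound of this kind relies on large-sample theory, and the planning values imply single-digit counts. Two failures are possible. With a rich model, an empty cell sends coefficients to infinity and the decisive rate difference may not exist. With a lean model the fit usually converges, but the interval is too narrow at such counts. The whole trial is decided on this one bound. Unless a rule for these cases is fixed beforehand, a repair would have to be chosen after counts by policy are known.

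**Working it through.** **Inputs.** From the article: 9,130 patient-days, 1 per 1,000, margin 1 per 1,000, one-sided 5%, two sites with four periods each, opposite sequences. Assumed: the same rate under SP when the policies are equal, equal patient-days per site-period, and no extra-Poisson variation unless stated.

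**The plan's own figures.** The article states: "Using a one-sided alpha of 5% and 80% power, a total of 6,178 patient-days were required". A one-sample expression gives (1.645 + 0.842)² × 0.001 × 0.999 / 0.001² = 6,176, which matches. The two-group formula has twice that variance: 12,353 per policy, 24,706 in total. The design effect gives 6,178 × 1.48 = 9,143, close to the stated 9,130.

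**Expected counts.** 9,130 × 0.001 = 9.13 acquisitions: 4.57 per policy and 2.28 per site-by-policy cell.

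**Why empty cells matter.** Season coincides with site apart from October and March. With a four-level order the model has six parameters (intercept, policy, season, three for order), or 9.13 / 6 ≈ 1.5 acquisitions per parameter. Policy is then identified only from how acquisitions split between sites within each order. With equal patient-days the policy coefficient is half the log of (SP at site A × SP at site B) / (CP at site A × CP at site B), where each term is a cell count. One empty cell makes it infinite, and the standardised rate difference diverges. A negative binomial model has the same mean structure and the same problem.

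P(at least one empty cell) = 1 − (1 − e^−2.28)⁴ = 35% at equal rates of 1 per 1,000.

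**Simulation** of the eight site-periods, both rates 1 per 1,000, 10,000 trials per coding:

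| Coding of period order | Some coefficient non-finite | Concludes non-inferiority | Same, non-finite counted as failure |
|---|---|---|---|
| Four-level factor | 49% | 25% | 18.5% |
| Two-level (first/second of a pair) | 35% | 26% | 24.5% |
| Linear | 4.6% | 45% | 43% |
| Absorbed by site (policy + season) | 4.1% | 46% | 43.5% |
| Score bound, no regression | always defined | 40% | – |

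Under four levels the rate difference itself diverges in about 35% of trials. In the other 14 points only nuisance terms diverge. The relative loss against the score bound is 1 − 24.9/40.3 = 38%, or 54% if a non-finite fit counts as failure. Splitting patient-days by beds (38 and 44) gives nearly the same result.

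**Error at the margin (1 versus 2 per 1,000).** Four-level about 4%; linear about 6%. With policy and season only and equal patient-days, the fit returns the crude policy rates, so the bound is the simple two-rate Wald bound. Its exact error at 4,565 patient-days per policy is 6.1%, against 5.1% for the score bound.

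**Between-period variation.** With gamma variation between site-periods, the site-stratified score bound has error of 4.9% at a coefficient of variation of 0, about 6% at 0.3 and 8.6% at 0.5.

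**Effect of size.** At 24,706 patient-days about 2% of four-level fits are non-finite, and power is 74% against 75% for the score bound.

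**The case against.** A reader might infer that the planned model fails in half of trials and gives up more than a third of its power whatever the coding. The document does not support that. It does not say how order enters, and its Fig 2 footnote and Randomization section use order for which policy comes first. Read that way, the term is aliased with site and only about 4% of fits are non-finite. Under that coding or a linear one, power is slightly above that of the score bound, partly because the Wald bound is too narrow. Half is also too strong for the decisive contrast under four levels, where the figure is about 35%; error there is below 5%.

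Nor can one infer that the analyst will have to improvise. An analysis plan that is not shown may fix the coding and the handling of empty cells, and the Discussion mentions pre-specified conservative modelling.

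It is also fair to say that the sparse counts come largely from the sample size, since the two analyses nearly agree at 24,706 patient-days, and that a score bound without variance inflation is itself anti-conservative when rates vary between periods.

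What stands is that the article itself commits the decision to a bound derived from the fitted model. At the planned size that bound performs poorly under each coding examined, though in different ways.

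**Conclusion.** The point holds in conditional form. With about nine expected acquisitions, the model-derived large-sample bound is a poor basis for the decision. If order is a four-level factor (and much the same for two levels), the policy contrast is undefined in about 35% of trials and the chance of concluding non-inferiority under equal policies falls to about 25%, against about 40%. If order is linear or absorbed by site, the cost is an error of about 6% instead of 5%.

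These figures rest on the planning rate, equal patient-days, Poisson counts and all eight scheduled periods. With both rates at 2 per 1,000, non-finite four-level fits fall to 8%. With a between-period coefficient of variation of 0.5 they rise to 58%. The 40% for the score bound is half the planned 80%; that shortfall is a separate error in the sample size.

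**What to change.** In Statistical methods:

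- Base the decision on a score-type (Miettinen-Nurminen) one-sided 95% upper bound for the SP minus CP rate difference, stratified by site with equal site weights. It stays defined with zero counts.
- Leave period-order terms out of this decision analysis. Stratifying by site largely holds season fixed. Because the sequences are opposite, additive order effects common to both sites enter the two site differences with opposite signs and cancel when patient-days are balanced.
- State in advance an explicit variance inflation for between-period overdispersion, with its size justified and applied to this bound.
- Keep the regression with season, period order and antibiotic exposure as supportive, and state how order is coded.
- In Sample size, restate the power: the change leaves it at about 40% at 9,130 patient-days, and variance inflation will lower it further.

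The analysis change costs wording only, and because the trial is ongoing it can be made before analysis. The downside is that unbalanced or non-linear calendar trends are examined only in the supportive model. Correcting the sample size is a separate decision with its own cost.

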## Introduction

### Background and rationale

Multidrug-resistant Gram-negative bacteria (MDR-GNB) pose a major global health challenge in the 21st century [1,2]. Since the early 2000s, the prevalence of third-generation cephalosporin–resistant Enterobacterales has steadily increased worldwide. Extended-spectrum β-lactamase–producing Enterobacterales (ESBL-E) are a major contributor to this rise [3], with numerous outbreaks reported in healthcare settings, particularly in intensive care units (ICU) and long-term care wards, leading to increased morbidity, mortality, and healthcare costs [4,5].

Initially, Klebsiella pneumoniae was the most frequently isolated ESBL-E species, but more recent epidemiological data indicate a growing burden of ESBL-producing Escherichia coli, especially in community settings [6]. In France, national surveillance data have shown a continuous increase in ESBL-E incidence, with incidence density rates now three to four times higher than those observed for methicillin-resistant Staphylococcus aureus (MRSA) [7].

Advanced age is a well-established risk factor for infection [8], largely due to immunosenescence and the high prevalence of chronic comorbidities [9–11]. A multicenter prevalence study conducted in eight French hospitals identified hospitalization in geriatric wards as a significant risk factor for ESBL-E carriage, with 28.2% of geriatric inpatients colonized [12]. Prolonged care and frequent exposure to biological fluids in geriatric settings further increase the risk of cross-transmission.

Elderly inpatients therefore present multiple risk factors for colonization with multidrug-resistant organisms (MDRO), including antibiotic exposure, colonization pressure, and organizational factors such as workload and care density. Several studies have demonstrated associations between staffing constraints, increased workload, and healthcare-associated infection risk [13,14]. Despite this, geriatric wards remain relatively understudied as potential reservoirs of ESBL-E.

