### Participants

#### Inclusion criteria.

Patients are eligible for inclusion if they meet all of the following criteria:

age ≥ 65 years;hospitalization in a participating geriatric unit during a study period;affiliation to a social security system;written informed consent obtained within 48 hours of admission, either from the patient or a legal representative.

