### Participant timeline

The participant timeline is detailed in Table 2.

**Table 2 pone.0353783.t002:** Participant timeline.

Study phase	Admission (≤48h after admission)	During hospitalisation	At discharge
Eligibility assessment	**X**		
Written informed consent	**X**		
Baseline rectal screening for ESBL-E carriage	**X**		
Routine clinical microbiology (if clinically indicated)		**X**	**X**
Documentation of antibiotic exposure		**X**	**X**
Monitoring of clinical status and adverse events		**X**	**X**
Discharge rectal screening for ESBL-E carriage			**X**
Assessment of ESBL-E acquisition (primary outcome)			**X**

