### Microbiological samples

Rectal swabs for ESBL-E surveillance cultures are obtained by trained ward nurses within 48 hours of admission and at discharge. Samples are processed in local microbiology laboratories following standardized procedures, including direct plating on chromogenic agar for ESBL-E detection. Antimicrobial susceptibility testing is performed using disk diffusion and interpreted according to CASFM–EUCAST guidelines.

All ESBL-E isolates are stored and sent to the Infection Control Department of Besançon University Hospital for molecular typing using pulsed-field gel electrophoresis. Laboratory staff performing molecular analyses are blinded to study period and IPC strategy.

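### Imported ESBL-E carriage, named as a risk factor and swabbed at admission in every participant, enters no model, so a carriage deviation in one site-period passes into the SP-CP estimate

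*Protocol article*

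**What the plan says.** The Background and rationale section says that elderly inpatients carry several risk factors for colonization, "including antibiotic exposure, colonization pressure, and organizational factors such as workload and care density".

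The Statistical methods section sets out the model. "Models will include fixed effects for intervention (SP vs CP), calendar period or season, and period order". It then adds one clinical covariate: "Additional adjusted analyses will include systemic antibiotic exposure during hospitalization as a covariate to account for antimicrobial pressure as a potential confounding factor". The Limitations and interpretation section repeats antibiotic exposure as the patient-level adjustment, and its caveat on residual confounding names only antimicrobial use and prescribing.

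Carriage at admission is collected under both policies. The Microbiological samples section states: "Rectal swabs for ESBL-E surveillance cultures are obtained by trained ward nurses within 48 hours of admission and at discharge". Table 2 lists "Baseline rectal screening for ESBL-E carriage" at admission. The primary outcome requires a negative admission screen, so imported carriers are kept out of the acquisition count. No section uses them as a measure of the exposure they create for other patients.

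**The concern.** Two drivers of acquisition are named side by side. One is adjusted for. The other is measured and left out.

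Acquisition by cross-transmission depends on how many carriers are on the ward. Each site compares SP with CP across different years, and a single draw fixes the order, so randomization over so few site-periods cannot be relied on to balance imported carriage. If the SP periods happen to receive fewer carriers, an inferior policy looks better than it is. If they receive more, an equivalent policy looks worse. A non-inferiority claim read from one difference in rates has no way to show which of these occurred.

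**Working it through.** The plan gives no figure of its own on this point, so the check asks what the planned terms remove and how large the remainder could be.

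**Inputs from the protocol article**
- Two sites with four periods each (Co-interventions), so 8 site-periods. Strict alternation is assumed, giving 4 CP and 4 SP.
- CP rate of 1 per 1,000 patient-days, margin of 1 per 1,000, one-sided 5%, 9,130 patient-days and 954 patients (Sample size).
- Carriage of 28.2% in geriatric inpatients (Background). This comes from other hospitals and is not an admission figure.

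**Assumptions not in the documents**
- Acquisition is proportional to imported carriage.
- Patient-days and patients split evenly between policies: t = 9.130/2 = 4.565 thousand patient-days and 954/2 = 477 patients each.
- Carriage varies between site-periods with a log-scale SD of 0.2 to 0.4 or, alternatively, an SD of 3 to 10 percentage points.
- There is no other extra-Poisson variation.

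**Step 1: what the planned terms remove.** On the 8 site-periods, season coincides with site. A design matrix with policy, site/season and four-level period order has rank 6, which leaves 2 residual degrees of freedom. The adjusted policy contrast gives each site-period a weight of +0.25 or -0.25. Differences common to both sites in a study year cancel, as do stable differences between sites. A deviation in one site-period keeps a quarter of its size in the estimate.

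**Step 2: size of a chance imbalance.** For log-SD s, the SD of the log SP/CP carriage ratio is s × sqrt(1/4 + 1/4) = 0.707s. This is 0.14 for s = 0.2 and 0.28 for s = 0.4, or factors of 1.15 and 1.33. On the percentage-point scale, the SD of the carriage difference is sqrt(2 × 0.282 × 0.718/477 + 2 × SD²/4). For a between-period SD of 0, 3, 5 and 10 points it is 2.9, 3.6, 4.6 and 7.7 points. Dividing by 0.282, at a rate of 1 per 1,000, gives a spurious rate difference with SD 0.10, 0.13, 0.16 and 0.27 per 1,000. The Poisson standard error at equal rates is sqrt(2 × 1/4.565) = 0.66 per 1,000.

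**Step 3: effect on the decision, given an imbalance.** Rule: (x_SP − x_CP)/t + 1.645 × sqrt(x_SP + x_CP)/t < 1, by exact Poisson enumeration. A carriage ratio r is applied by dividing one policy's rate by sqrt(r) and multiplying the other's by sqrt(r).

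| True rates SP, CP | Balanced | r = 1.25 | r = 1.5 |
|---|---|---|---|
| 2, 1 (at the margin), fewer carriers in SP | 6.1% | 12.5% (1.79 vs 1.12) | 20.2% (1.63 vs 1.22) |
| 1, 1, more carriers in SP | 46% | 34% | 25% |
| 1, 1, fewer carriers in SP | 46% | 59% | 69% |

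Entries are the chance of declaring non-inferiority.

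**Step 4: averaged over random imbalance.** With SP at the margin, the chance is 6.7% for s = 0.2 and 8.3% for s = 0.4, against 6.1%. The percentage-point version, by simulation, gives 6.4%, 6.8% and 8.5% for SDs of 3, 5 and 10 points, against 6.0%. With equal policies the average stays near 46%. A harmful imbalance of at least 1.5-fold has probability 0.2% at s = 0.2 and 7.6% at s = 0.4.

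**Step 5: more patient-days do not remove it.** At 24,706 patient-days the simulated false non-inferiority rate is 5.5% with no between-period variation, and 6.1%, 7.0% and 10.9% for SDs of 3, 5 and 10 points.

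**The case against.** The strongest reply is that chance imbalance of either sign is between-period variance, not directional bias. The plan acknowledges clustering through a design effect of 1.48 and a negative binomial option, and it concedes that two clusters limit causal inference. Averaged over plausible imbalances, the error rate moves little. This stands, and it is why the point supports a sensitivity analysis and not a new primary model.

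Three stronger readings are not supported:
- A reader might infer that antibiotic exposure is the only adjustment. It is not: calendar period or season and period order are also in the models, and they absorb shared and stable carriage differences.
- A reader might infer that carriage is known for every admission. Enrolment requires "written informed consent obtained within 48 hours of admission, either from the patient or a legal representative", and stays under four days are excluded. About 9,130 participant-days compare with roughly 82 beds × 4 × 183 days = 60,024 bed-days (full occupancy assumed), so the swabs only sample ward carriage.
- A reader might take 12% or 20% as the trial's error rate. Those figures hold only once a harmful imbalance of the stated size has occurred.

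It can also be said that a separate analysis plan may add this covariate, and that the Limitations section mentions sensitivity analyses. That is possible. However, the Statistical methods section itself chooses which named risk factor to carry into the adjusted analyses, and the sensitivity analyses are not described.

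**Conclusion.** The concern holds in a limited form. Imported carriage is a named risk factor, is measured in every participant under both policies, and enters no model. The planned terms leave single-site-period deviations in the SP-CP estimate. Under the assumptions above, the spurious difference has an SD of about 0.1 to 0.3 per 1,000, against a margin of 1 and a sampling error of 0.66. False non-inferiority at the margin rises on average from about 6% to 6.5-8.5%. Neither the proportionality of acquisition to carriage nor the between-period variation can be taken from the documents, and the sign of any real imbalance is unknown. The documents do not show that the comparison is biased toward either policy. The change is worth making because the data are already collected, and an adjustment chosen after the results are known would be open to challenge.

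**What to change.** In the additional adjusted analyses under Statistical methods:

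1. Pre-specify a sensitivity analysis that adds imported colonization pressure as a covariate with an estimated coefficient. Define it as the share of admission-swabbed participants who are positive, from admission swabs only, because discharge results are affected by the policy. Calculate it by unit and a time window wide enough to avoid empty cells. Unit by month gives 2 × 28 + 4 × 24 = 152 cells with about 6 participants each. At 28.2% prevalence about 12% of these would have no positive swab, and at an assumed 15% about 36%. Unit by study period gives 6 × 4 = 24 cells with about 40 each.
2. Do not enter log prevalence as an offset. That forces the coefficient to 1 and is undefined in cells with no positive swab. It can also add error. At an assumed 15% prevalence, sampling error of the log SP/CP ratio is sqrt(2 × 0.85/(0.15 × 477)) = 0.15. If half of acquisition is carriage-driven and s = 0.2, the residual is sqrt(0.07² + 0.15²) = 0.17 with the offset, against 0.07 with no adjustment.
3. Report admission ESBL-E prevalence by policy and site-period beside the primary result.
4. State that a non-inferiority conclusion that changes under this analysis will be reported as not robust.

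The cost is wording and some programming, with no new data. The adjustment is partial, because participants only sample ward carriage. It will also be imprecise: 9,130 patient-days give about 9 expected events at equal rates (9.13 × 1) and about 14 at the margin (4.565 × 3). It should therefore stay a sensitivity analysis and not replace the primary model.
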